## Abstract

**Introduction:**

Lung cancer is a leading cause of cancer deaths worldwide and surgery remains the main treatment for early stage disease. Prior to the introduction of video-assisted thoracoscopic surgery (VATS), lung resection for cancer was undertaken through an open thoracotomy. To date, the evidence base supporting the different surgical approaches is based on non-randomised studies, small randomised trials and is focused mainly on short-term in-hospital outcomes.

**Methods and analysis:**

The VIdeo assisted thoracoscopic lobectomy versus conventional Open LobEcTomy for lung cancer study is a UK multicentre parallel group randomised controlled trial (RCT) with blinding of outcome assessors and participants (to hospital discharge) comparing the effectiveness, cost-effectiveness and acceptability of VATS lobectomy versus open lobectomy for treatment of lung cancer. We will test the hypothesis that VATS lobectomy is superior to open lobectomy with respect to self-reported physical function 5 weeks after randomisation (approximately 1 month after surgery). Secondary outcomes include assessment of efficacy (hospital stay, pain, proportion and time to uptake of chemotherapy), measures of safety (adverse health events), oncological outcomes (proportion of patients upstaged to pathologic N2 (pN2) disease and disease-free survival), overall survival and health related quality of life to 1 year. The QuinteT Recruitment Intervention is integrated into the trial to optimise recruitment.

**Ethics and dissemination:**

This trial has been approved by the UK (Dulwich) National Research Ethics Service Committee London. Findings will be written-up as methodology papers for conference presentation, and publication in peer-reviewed journals. Many aspects of the feasibility work will inform surgical RCTs in general and these will be reported at methodology meetings. We will also link with lung cancer clinical studies groups. The patient and public involvement group that works with the Respiratory Biomedical Research Unit at the Brompton Hospital will help identify how we can best publicise the findings.

**Trial registration number:**

ISRCTN13472721

Strengths and limitations of this studyFirst multicentre randomised trial on this topic.All surgeons carry out both interventions; the randomisation scheme ensures surgeon balance across the groups to minimise performance bias.Masking of the incision and evaluation of the success of blinding.Procedures reflective of UK practice (majority are postero-lateral thoracotomy).Surgeon crossovers (ie, surgeon changes after randomisation) can occur in centres with pooled service provision.

## Introduction

### Background and objectives

Lung cancer is a leading cause of cancer death worldwide and survival in the UK remains among the lowest in Europe. Surgery, conventionally undertaken through an open thoracotomy for lung resection, remains the treatment for early stage disease. The randomised trial comparing lobectomy with limited resection (segment or wedge), published in 1995 concluded that lobectomy should be the surgical procedure for patients with lung cancer.^1^ The only grade 1 evidence published since is a post-hoc analysis of the CALGB/Alliance 140 503 trial in patients with peripheral non-small-cell lung cancer, which concluded that lobar and sublobar resection had similar perioperative mortality and morbidity outcomes.^2^ Since the introduction of minimal access video-assisted thoracoscopic surgery (VATS) techniques, lung cancer resection undertaken through a VATS approach increased from 14% in 2010 to 40% in 2014 in the UK.^3^

Much of the evidence generated to date is based on non-randomised studies^4 5^ or small randomised trials focusing on short-term (in-hospital) outcomes,^6^ that are underpowered to detect differences in longer term outcomes such as survival^7^ or have focused solely on operative technique.^8^ Currently, the most well-designed randomised controlled trial (RCT) by Bendixen *et al*, reported shorter hospital stay and less pain in patients randomised to VATS lobectomy.^9^ In this study, all patients received epidural anaesthesia and anterior thoracotomy for open surgery which is not the current practice for most thoracic surgery centres in the UK. In contrast, a recent trial by Hao et al from China, published in 2018, reported a similar hospital stay in the VATS and axillary thoracotomy groups.^10^ In addition, little high quality randomised data has been published to ascertain the cost effectiveness (ie, quality of life and costs) for VATS, highlighted in a follow-up report by Bendixen *et al* and an on-going trial in France (Lungsco1) that will specifically compare VATS lobectomy versus open thoracotomy from an economic cost to society perspective.^11 12^

A well designed and conducted RCT comparing the effectiveness and cost-effectiveness of minimal access and open surgery is needed to inform current UK (National Health Service; NHS) practice, health policy and individual surgeon and patient decision-making.

The VIdeo assisted thoracoscopic lobectomy versus conventional Open LobEcTomy for lung cancer (VIOLET) study is a UK multicentre pragmatic RCT comparing the effectiveness, cost-effectiveness and acceptability of VATS lobectomy versus open lobectomy for treatment of lung cancer.

### Aims and objectives

The VIOLET study will test the hypothesis that VATS lobectomy is superior to open lobectomy with respect to self-reported physical function 5 weeks after randomisation (approximately 1 month after surgery).

Specific objectives are to estimate:

The difference between groups in the average self-reported physical function at 5 weeks.The difference between groups with respect to a range of secondary outcomes including assessment of efficacy (hospital stay, pain, proportion and time to uptake of chemotherapy), measures of safety (adverse health events), oncological outcomes (proportion of patients upstaged to pN2 disease and disease-free survival) and overall survival.The cost-effectiveness of VATS lobectomy compared with open lobectomy.

## Methods

### Trial design

A UK-based multicentre parallel group RCT with blinding of outcome assessors and participants until hospital discharge after surgery. Figures 1 and 2 show the expected patient pathway for both phases of recruitment to the VIOLET study.

**Figure 1 F1:**
[figure not shown]
The trial schema showing the recruitment pathway for phase 1 (pilot phase) of the VIOLET study. VATS, video-assisted thoracoscopic surgery; VIOLET, VIdeo assisted thoracoscopic lobectomy versus conventional Open LobEcTomy for lung cancer.

**Figure 2 F2:**
[figure not shown]
The trial schema showing the recruitment pathway for phase 2 of the VIOLET study. VATS, video-assisted thoracoscopic surgery; VIOLET, VIdeo assisted thoracoscopic lobectomy versus conventional Open LobEcTomy for lung cancer.

*Phase 1:* The first phase with an integrated qualitative component is necessary to establish the processes for recruitment and consent. This phase is also essential to develop a study manual and a measure of surgical expertise to proceed to phase 2. Phase 1 will be conducted in five centres; Royal Brompton Hospital in London, The University Hospitals Bristol in Bristol, Liverpool Heart and Chest Hospital in Liverpool, The James Cook University Hospital in Middlesbrough and Harefield Hospital in Harefield. These centres are well spread geographically and represent a mix of university and NHS trusts that are representative of NHS practice. Progression from pilot to the full trial will be dependent on preagreed progression criteria (assessed after 18 months of recruitment):

Specifically:

At least 60% of patients undergoing lobectomy are considered eligible for the trial (if necessary, by revising the eligibility criteria).At least 50% consent to randomisation after 6 months of recruitment.Less than 5% fail to receive their allocated treatment.Less than 5% lost to follow-up, excluding deaths.

*Phase 2:* This phase will extend the study to up to a further five centres. All centres will use the optimum methods of recruitment established in phase 1 and will follow-up all participants to 1 year.

### Study population

Participating *centres* will only be eligible if they meet all the following eligibility criteria: (1) NHS Trust with an established and accredited lung cancer multi-disciplinary team (MDT). (2) Centre carries out ≥40 VATS lobectomies each year and employs at least one surgeon who has carried out ≥50 VATS lobectomies.

Participating *surgeons* will be eligible for the trial if they have performed ≥50 VATS lobectomies. Prospective surgeons will be required to submit their activity logs, which will be validated against local audit data from the MDT meetings, prior to acceptance to the trial. Lobectomy via open surgery is currently standard procedure and therefore surgical ability and competence will be assured by specialist UK General Medical Council (GMC) registration.

*Patients* may enter the study if all the following apply:

Adult aged ≥16 years of age.Able to give written informed consent, undergoing either: (a) lobectomy or bilobectomy for treatment of known or suspected primary lung cancer beyond lobar orifice* in tumour, node, metastases TNM8 stage cT1-3 (by size criteria, equivalent to TNM7 stage cT1a-2b) or cT3 (by virtue of 2 nodules in the same lobe), N0-1 and M0 or (b) undergoing frozen section biopsy with the intention to proceed with lobectomy or bilobectomy if primary lung cancer with a peripheral tumour beyond a lobar orifice* in TNM8 stage cT1-3 (by size criteria, equivalent to TNM7 stage cT1a-2b) or cT3 (by virtue of 2 nodules in the same lobe), N0-1 and M0 is confirmed.Disease suitable for both minimal access (VATS lobectomy) and lobectomy via open surgery.

*In the case of bilobectomy, the distance for the ‘lobar’ orifice is in reference to the bronchus intermedius.

*Patients* may not enter the study if any of the following apply:

Previous malignancy that influences life expectancy.Pneumonectomy, segmentectomy or non-anatomic resection (eg, wedge resection) is planned.Patient has a serious concomitant disorder that would compromise patient safety during surgery.Planned robotic surgery.

### Randomisation

Participants will be randomised in a 1:1 ratio to either VATS lobectomy or open lobectomy. Randomisation will take place through a secure internet-based randomisation system, access to which will be restricted to authorised study personnel. Cohort minimisation (with a random element incorporated) will be used to ensure balance across groups with respect to the surgeon and the allocation will be stratified by centre.

Due to the pragmatic nature of this trial there will inevitably be some variability between surgeons, the surgical teams and the perioperative processes. Such heterogeneity is important as this accurately reflects real clinical practice.

Randomisation will be performed 1 week prior to the planned operation date, once eligibility has been confirmed and written consent taken by a research nurse. This will allow sufficient time for operating theatre schedules to be arranged. If there is a change in surgeon after randomisation, the analysis will account for the surgeon responsible for performing the operation and not the surgeon originally allocated to the patient.

### Trial interventions

All operations will be undertaken with general anaesthesia and with the patient in the lateral decubitus position.

VATS lobectomy is undertaken through one to four keyhole incisions without rib spreading. The use of ‘rib spreading’ is prohibited as this is the key intra-operative manoeuvre which disrupts tissues and causes pain (and is used in open surgery). The procedure is performed with videoscopic visualisation without direct vision. The hilar structures are dissected, stapled and divided. Endoscopic ligation of pulmonary arterial branches may be performed. The fissure is completed and the lobe of lung resected. The incisions are closed in layers and may involve muscle, fat and skin layers. This definition of VATS lobectomy is a modification of Cancer and Leukaemia Group B (CALGB) 39 802.^13^

Conventional open lobectomy is undertaken through a single incision with or without rib resection and with rib spreading. The operation is performed under direct vision with isolation of the hilar structures (vein, artery and bronchus) which are dissected, ligated and divided in sequence and the lobe of lung resected. The procedures may be undertaken using ligatures, over sewing or with staplers. The thoracotomy is closed in layers starting from pericostal sutures over the ribs, muscle, fat and skin layers.

In both groups, lymph node management is undertaken in accordance with the International Association of the Study of Lung Cancer recommendations where a minimum of six nodes/stations are removed, of which three are from the mediastinum that includes the subcarinal station.^14^

Because this is a pragmatic trial, adaptations and variation in both procedures (with the exception of the mandated elements outlined above) will be permitted although intraoperative details will be collected, and compliance monitored.

### Primary and secondary outcomes

The primary outcome is self-reported physical function measured using the European Organization for Research and Treatment of Cancer Quality of Life Questionnaire-C30 (EORTC QLQ-C30) at 5 weeks post-randomisation. Physical function has been chosen because it is a patient-centred outcome that will reflect the anticipated earlier recovery with VATS lobectomy and has been used in other minimal access surgery trials. The primary endpoint has been chosen to be 5 weeks (1 month post-surgery) to capture the early benefits of minimal access surgery on recovery. The EORTC QLQ-C30 has been validated for use in European cohorts. In addition to assessing physical function the questionnaire also assesses psychological and social well-being. Secondary outcomes have been selected to assess the efficacy of the two approaches.

Secondary outcomes are (1) time from surgery to hospital discharge; (2) adverse health events; (3) proportion and time to uptake of adjuvant treatment; (4) proportion of patients upstaged to pN2 disease after the procedure; (5) overall and disease-free survival to 1 year; (6) proportion of patients who undergo complete resection during the procedure; (7) proportion of patients who experience prolonged incision pain defined as the need for analgesia >6 weeks after surgery; (8) generic and disease-specific health-related quality of life (HRQoL) assessed using the EORTC QLQ-C30, QLQ-LC13 and EQ-5D-5L questionnaires completed at 2 weeks, 5 weeks, 3 months, 6 months and 1 year post-randomisation); (9) resource use measured for the duration of post-operative hospital stay until discharge and at 5 weeks, 3 months, 6 months and 1 year post-randomisation.

### Data collection

The schedule of data collection for the study is shown in table 1. Data will be collected on paper and then entered onto a bespoke database. Access to the database will be via a secure password-protected web-interface (NHS clinical portal). Study data transferred electronically between the University of Bristol and the NHS will only be transferred via a secure NHS.net network in an encrypted form.

**Table 1 T1:** Data collection for trial participants who agree to randomisation to VATS lobectomy or open lobectomy

	Pre-randomisation	Post-randomisation								
	Baseline	Day of surgery	Postop	2 days postop	Discharge	2 weeks*	5 weeks*	3 months*	6 months*	1 year*
Eligibility	*X*									
Imaging review (CT/Positron Emmission Tomography (PET)--CT†)	*X*									
Participant characteristics	*X*									
Audio recorded consultation	*X*									
Lobectomy via VATS lobectomy or open lobectomy		*X*								
Intraoperative details		*X*								
Histopathology staging		*X*								
Tumour sample for research		*X*								
Patient questionnaires										
QLQ-C30	*X*					*X*	*X*	*X*	*X*	*X*
QLQ-LC13	*X*					*X*	*X*	*X*	*X*	*X*
EQ5D	*X*					*X*	*X*	*X*	*X*	*X*
Bang Blinding Index				*X*	*X*					
Pain score	*X*		*X*	*X*						
Adverse events		*X*					*X*	*X*	*X*	*X*
Resource use	*X*	*X*					*X*	*X*	*X*	*X*
CT scan of chest and abdomen										*X*

*Follow-up time-points will be calculated from the date of randomisation.

†Review of images available from staging scans performed in accordance with standard practice at participating centres.

QLQ, Quality of Life Questionnaire; VATS, video-assisted thoracoscopic surgery.

### Blinding of staff and study participants

The operating surgeon and staff responsible for the care of the participant during the operation cannot be blinded to the participants’ treatment allocation. However, in order to minimise the risk of bias, attempts will be made to blind the research nurse responsible for the collection of follow-up data. Specifically, randomisation will be performed by a member of the research team who is not responsible for the collection of follow-up data for VIOLET study participants.

Furthermore, efforts will be made to minimise the risk of inadvertent unblinding of the research nurse responsible for data collection during the patient’s postoperative stay. To accomplish this, large adhesive dressings will be applied to thorax. These adhesive dressings will be positioned similarly for all participants, regardless of their surgical allocation and will cover both real and potential incision/port locations. The initial adhesive dressings will be applied in the operating theatre by the operating team and these will not be changed until 3 days after surgery (or discharge if discharged before day 3), unless soiling or lack of adherence prompts their premature replacement. Three days after surgery, dressings will be changed by a nurse who is not responsible for conducting the participants’ follow-up assessments. Wound cleaning will be performed on all real and potential incision/port locations to promote allocation masking.

Patients who agree to participate in the RCT will not be informed of their treatment allocation until they are discharged from hospital after their operation. In order to ensure that study patients are not unblinded during wound cleaning and dressing change, participants will be asked to turn their head away from the wound site that is being tended to. When participants are considered ‘fit-for-discharge’, they will be informed of their treatment allocation and advised as to how best to care for their surgical wounds. Blinding in surgical trials are considered challenging yet an important aspect to reduce bias, patient drop-out and increase the validity of results.^15–17^ Participants are made aware at consent that they will not be informed of their treatment allocation until after their surgery. Blinding was approved by the research ethics committee.

The success of blinding will be monitored during each participant’s in-hospital stay. Participants will be asked to complete the Bang-blinding Index^18^ at 2 days postoperatively and at discharge, but before the treatment allocation is revealed. The research nurse responsible for data collection and follow-up of VIOLET study participants will also be asked to complete the Bang-blinding Index when the participant is ready for discharge and after the participant attends for their 5-week and 1-year follow-up appointments.

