### Standardisation of postoperative management

As this is a pragmatic RCT, postoperative care and the criteria for drain removal will be in accordance with local practice. However, we have identified two elements of patient care, which require standardisation to minimise the potential for bias, namely pain-control and the criteria by which a participant’s medical fitness-for-discharge is assessed.

Standardising the use of analgesia across participating centres is impractical and does not reflect the intended pragmatic nature of the trial, it, would also produce data unrepresentative of real clinical practice. Therefore, each participating centre will prescribe analgesia in accordance with their local protocols. All patients recruited to the RCT at that centre will be given the same analgesia regardless of their treatment allocation (ie, VATS lobectomy or open lobectomy). Local protocols for the provision of analgesia will be defined by the local Principal Investigator (in collaboration with the local research team) prior to the start of recruitment to the RCT. Analgesia administered throughout the participant’s in-hospital stay will be recorded on the trial case report forms (CRFs) and compliance with the predefined and centre-specific analgesia protocols will be monitored.

In order to objectively compare the time from surgery to hospital discharge between VATS lobectomy and open lobectomy, the following discharge suitability criteria have been developed. Study participants will be evaluated against these criteria to ensure that they are medically fit-for-discharge:

Participant has achieved satisfactory mobility.Pain under control with analgesia.Satisfactory serum haemoglobin and electrolytes (ie, does not require intervention).Satisfactory chest X-ray (which will be performed as part of routine clinical care).No complications that require further/additional treatment.

Participants who are considered medically fit-for-discharge may not necessarily be discharged immediately; in some instances, social and other factors may necessitate extended hospitalisation. The time at which participants are considered medically fit-for-discharge and when they are physically discharged from hospital will both be recorded on the trial CRFs.

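### Allocation is revealed either at discharge or at the earlier fit-for-discharge decision; under the second rule some participants are unblinded before the length-of-stay outcome occurs

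*Protocol article*

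**What the plan says.** The Trial design section promises "blinding of outcome assessors and participants until hospital discharge after surgery", and the abstract says the same. Under Blinding of staff and study participants, the article first states that trial patients "will not be informed of their treatment allocation until they are discharged from hospital after their operation". Later in the same paragraph it ties the disclosure to a different moment: when participants are considered fit for discharge, "they will be informed of their treatment allocation and advised as to how best to care for their surgical wounds".

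Standardisation of postoperative management lists five criteria for medical fitness and then separates fitness from leaving hospital: "Participants who are considered medically fit-for-discharge may not necessarily be discharged immediately", because "in some instances, social and other factors may necessitate extended hospitalisation". Both times go on the case report form.

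Under Primary and secondary outcomes, the first secondary outcome is "time from surgery to hospital discharge". The blinding section also asks participants to complete the Bang index two days after surgery and again at discharge, the latter ahead of the disclosure.

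**The concern.** Participant blinding is claimed up to hospital discharge, and the length-of-stay clock stops at that same event. If disclosure happens when fitness is judged, the masking ends earlier for anyone who stays on. The exposed part of the stay is the part after medical criteria have been met, where a participant's expectations could in principle have some influence on when they go home. Two things are at stake:

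- whether length of stay can be described as observed under participant blinding. It is the only secondary outcome given a target effect and a stated power;
- whether the discharge-time Bang index measures blinding, or is filled in by someone who has just been told the answer.

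Sites reading the two sentences differently could also disclose at different moments.

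**Working it through.** The point concerns the order of events, so the check sets the statements side by side. Write F for the time fitness is judged, D for physical discharge, and g = D − F for the gap.

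1. **Are F and D one event?** No. F is defined by listed criteria, the article says D may follow later, and both are recorded. So g is at least 0, and is above 0 for some participants.

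2. **Which event ends the outcome?** D, from the wording of the first secondary outcome.

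3. **Participant blinding over the interval from surgery to D:**
   - reveal at D: blinded throughout;
   - reveal at F with g = 0: blinded throughout, so the two rules coincide;
   - reveal at F with g > 0: blinded up to F, unblinded for the whole of g, and the outcome occurs after the reveal.

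4. **Can the Bang index be completed as described?** It must be at discharge and before the reveal. With the reveal at D, both conditions can be met. With the reveal at F and g > 0, a form completed at D comes after the reveal, and a form completed before the reveal is not at discharge. Both conditions cannot hold.

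5. **Size.** Let p be the share of an arm with g > 0, and d the average change in their discharge time caused by knowing the allocation. That arm's mean stay moves by p × d, and the between-arm difference moves by p(VATS) × d(VATS) − p(open) × d(open). An earlier discharge cannot exceed g. The article gives no value for p, d or g, so neither the size nor the direction can be calculated. The shift is zero if knowledge has no effect or acts equally in both arms. It would also be a shift in means, whereas the target is stated as medians of 3 and 4 days and a hazard ratio of 1.3.

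6. **Does it affect the planned power?** No. The article's length-of-stay statement is 80% power with 498 participants and 2% not surviving to discharge. Assuming a two-sided 5% level, which the sample size section does not state, the events are 498 × 0.98 = 488. By the Schoenfeld formula, power = Φ(√488 × ln 1.3 / 2 − 1.96) = Φ(2.898 − 1.960) = Φ(0.938) = 82.6%. That is slightly above the stated 80%, and nothing in it depends on when allocation is disclosed.

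7. **Does it affect the primary outcome?** No. Physical function is reported 5 weeks after randomisation, about a month after surgery. Against planned median stays of 3 and 4 days, participants will ordinarily have been told by then under either rule.

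**The case against.** The strongest reply is that this is loose wording with little consequence. Fitness is judged against common criteria before the participant is told under either sentence, so the medically determined part of the stay is masked from the participant in any case. Because both times are recorded, the exposed part can be measured. The article attributes longer stays to circumstances that make them necessary, which suggests constraint more than patient choice. The operating surgeon knows the allocation throughout, so knowledge of it could reach discharge decisions whichever rule applies. The article also already puts the Bang index ahead of the disclosure.

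Most of this stands, and it limits the weight of the point. It does not remove the contradiction: the article itself treats fitness and discharge as different events, and its ordering of the index and the disclosure works at discharge only if the disclosure also waits until discharge.

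Three stronger readings are tempting and are not supported:

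- **A reader might infer that a sizeable part of the one-day target could be an artefact.** That needs a share with a gap, a size of response and opposite directions in the two arms, none of which the article gives.
- **A reader might infer that the research nurse is unblinded too.** No statement says that the nurse is told or decides on discharge; an unblinded participant talking to the nurse is conjecture.
- **A reader might infer that the outcome must be redefined as time to fitness.** That would exchange an observed event for a judged one, and it is unnecessary once disclosure is moved.

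**Conclusion.** The concern holds as an internal contradiction with a limited consequence. The blinding section gives two disclosure times, and only the later one agrees with the abstract, the Trial design section and the timing of the Bang index. If sites follow the earlier one, participants with a gap between fitness and discharge are unblinded before the first secondary outcome occurs, and their discharge blinding check may be invalid.

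The possible bias has no size that can be derived from the article. It is confined to participants with a gap, acts only during that gap, and would add to any influence of surgeons who are unblinded throughout. The sample size and the primary outcome are untouched. The conclusion assumes only that some participants have a gap, which the article itself anticipates. The point is worth correcting because the correction is nearly free and restores the blinding that the article claims.

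**What to change.** Reconcile the two sentences in the blinding section with the abstract, the Trial design section and the Bang index timing: allocation is disclosed only at physical discharge, after the participant has completed the index. Keep time from surgery to physical discharge as the first secondary outcome.

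Report time from surgery to fitness for discharge as a supportive analysis. It ends before disclosure to the participant under either sentence, so it also covers participants already treated, whichever rule their site followed. It does not remove any influence of unblinded clinical staff on the fitness judgement.

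The cost is a wording change and a reminder to sites. No new data are needed, since both times are already collected, and the sample size does not change. The one downside is practical: wound-care advice that depends on the allocation moves to the point of leaving, so sites need to allow time for it then.
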